### Statement of Compliance

This document is a protocol for a research project. This study will be conducted in compliance with all stipulation of this protocol, the conditions of the ethics committee approval, the NHMRC National Statement on ethical Conduct in Human Research (2007) and the Note for Guidance on Good Clinical Practice (CPMP/ICH-135/95).

[figure not shown]

**\*\*This is the original ethics-approved protocol for the entire MINDSET study. Study 2 is the protocol specifically for the MINDSET trial.\*\***

## 82 Study synopsis

|                               |                                                                                                                                                                                                                                                                                                                                                                                                                                                                                                                                                                                                                                                                                                                                                                                                                                                                 |
|-------------------------------|-----------------------------------------------------------------------------------------------------------------------------------------------------------------------------------------------------------------------------------------------------------------------------------------------------------------------------------------------------------------------------------------------------------------------------------------------------------------------------------------------------------------------------------------------------------------------------------------------------------------------------------------------------------------------------------------------------------------------------------------------------------------------------------------------------------------------------------------------------------------|
| Title:                 | Improving interpreting for dementia assessments: The MINDSET Study                                                                                                                                                                                                                                                                                                                                                                                                                                                                                                                                                                                                                                                                                                                                                                                              |
| Short title:           | MINDSET                                                                                                                                                                                                                                                                                                                                                                                                                                                                                                                                                                                                                                                                                                                                                                                                                                                         |
| Study centres:         | National Ageing Research Institute, universities, and interpreting services                                                                                                                                                                                                                                                                                                                                                                                                                                                                                                                                                                                                                                                                                                                                                                                     |
| Study aim:             | To develop, user-test, evaluate, and implement online dementia assessment training for language interpreters.                                                                                                                                                                                                                                                                                                                                                                                                                                                                                                                                                                                                                                                                                                                                                   |
| Primary objectives:    | 
 
1. To improve the quality of interpreter communication in cognitive assessment for dementia.
 
2. To implement the training in Victoria, assessing for scalability and services' satisfaction.
 
                                                                                                                                                                                                                                                                                                                                                                                                                                                                                                                                                                                                         |
| Design:                | 
Study 1: Co-design the online training modules with interpreters, clinicians and carers of Culturally and Linguistically Diverse (CALD) people with dementia (Aim 1).
 
Study 2: Undertake a national randomised control trial (RCT) with 150 interpreters to assess in the impact of online training on the quality of interpreter communication in comparison to wait-list control (Objective 1).
 
Study 3: Implement the training in Victoria focusing on scalability, and assess services' satisfaction with the training via qualitative interviews with interpreters, managers, and clinicians to (Objective2).
                                                                                                                                                                                                    |
| Outcomes:              | Study outcomes realise a key priority in the NHMRC's National Institute of Dementia Research CALD Action Plan, which is to, "Inform effective ways to train frontline ... staff on how culture influences dementia." With a >200% projected growth in the proportion of older CALD Australians by 2056, there will be a rise in the number of non-English speaking people living with dementia. The national benefit of this study is that it will enable interpreters to be prepared and confident in performing their role impartially, effectively, and accurately. The training would ultimately sit on the National Accreditation Authority for Translators & Interpreters (NAATI) website and provide opportunity for every interpreter working with older CALD Australians to access training in interpreter mediated cognitive assessment for dementia. |
| Safety considerations: | Informed consent required from all participants.                                                                                                                                                                                                                                                                                                                                                                                                                                                                                                                                                                                                                                                                                                                                                                                                                |

83

84

85 **Glossary of abbreviations and terms**

| Abbreviation/term | Description                                                                               |
|-------------------|-------------------------------------------------------------------------------------------|
| Interpreter       | Person working professionally in the capacity of providing language interpreting services |
| RCT               | Randomised control trial                                                                  |
| NARI              | National Ageing Research Institute                                                        |
| NHMRC             | National Health and Medical Research Council                                              |
| NAATI             | National Accreditation Authority for Translators and Interpreters                         |
| AUSIT             | Australian Institute of Interpreters & Translators                                        |
| CALD              | Culturally and Linguistically Diverse                                                     |
| CPD               | Continuing Professional Development                                                       |
| CDAMS             | Cognitive Dementia & Memory Service                                                       |
| ACAS              | Aged care assessment service                                                              |
| PICF              | Participant Information and Consent Form                                                  |
| HREC              | Human Research Ethics Committee                                                           |
| CI                | Chief investigator                                                                        |

86

87

# 1 Introduction and background

## 1.1 *Lay summary*

This project will develop, test and implement a training course (“MINDSET”) for language interpreters who work with people living with dementia, or interpret for cognitive testing. Aged care assessment guidelines require that an interpreter be present when older people from non-English backgrounds undertake a cognitive test and interpreting for these assessments makes up a significant portion of many interpreters’ work schedule. However, interpreters can face challenges with the terminology of cognitive tests as well as working with older clients whose communication skills are affected by dementia or cognitive impairment. We will therefore develop a National Accreditation Authority for Translators and Interpreters (NAATI) accredited training course aimed at improving interpreters’ competence and confidence in this. The project consists of three studies, over three years.

During the first study, we will co-design the material for the training course with relevant stakeholders and then conduct user-testing of the finished course with interpreters. We will invite ~25 participants, including interpreters, clinicians, people living with dementia, and family carers, to participate in two workshops, over two days. The research team will design the course based on input from these workshops and based on what we know from other research. Once developed, the course will consist of 3-5 modules, take interpreters 3-4 hours to complete, and be accessible online through the NAATI website. We will also design course assessments, which will involve both quizzes and simulated interactions of cognitive assessments. Ten interpreters will take the course and assessments and provide feedback to the researchers for further refinement.

The second study will be a RCT (randomized control trial) to measure whether the training course improves interpreters’ performance when interpreting for cognitive assessments. The trial will involve two groups of 75 interpreters (150 in total), recruited through our interpreting industry partners and then randomly assigned to each group. The intervention group will undertake the training and the control group will not receive the training until after the trial is over. Interpreters from both groups’ will be assessed at three intervals, at the beginning of the trial (baseline), after 3-months (post-intervention) and after 6-months (follow up). The assessment will involve a 40-minute simulation of a cognitive assessment and questionnaires about medical terminology, ethics, medical interpreting, and cross-cultural communication. We will combine each interpreters’ assessment results at each interval into a composite score. We will then statistically analyse whether there is an improvement in performance after doing the training, as well as differences between the intervention and control groups.

The third study will be an implementation of the training course, which will make it available to all Victorian interpreters. Lessons from this study will guide our national implementation strategy. We will monitor training uptake with a target of 70% of eligible Victorian interpreters completing the course. After 50% of our target (i.e. 35% of eligible Victorian interpreters have done the training) is complete, we will conduct ~20-30 interviews with interpreters and interpreting agency managers to discuss training uptake, barriers and facilitators to the training, and the effect on interpreters’ work practices. We will also interview ~20 clinicians who frequently work with people with dementia from CALD

backgrounds to understand how the interpreters' training has influenced their work practices and their experiences with interpreters.

## 1.2 *Introduction*

This project will develop the first dementia assessment training for interpreters in Australia. The training aims to improve interpreters' competence and confidence in working with older people undertaking cognitive assessments, and thereby facilitate better accuracy of assessments. By extension, this aims to facilitate timely diagnosis of dementia among Australia's ageing culturally and linguistically diverse (CALD) populations and improve access to dementia-related services for older people from CALD backgrounds.

We will co-design with interpreters, clinicians, people with dementia and their carers online training modules for interpreters. These training modules will: describe dementia and its impact on cognitive and linguistic ability; explain the tools used to assess and diagnose dementia; and engage interpreters with effective interpreting strategies for cognitive assessments. The impact of the training on interpreter's quality of communication will be evaluated using a randomised controlled trial.

The key objectives of this project are to:

- Improve the quality of interpreter communication in cognitive assessment for dementia.
- Implement the training in Victoria to plan for national scale-up.

To achieve the objectives of this project, we will conduct three studies over three years, in which we will:

- 1) Co-design with stakeholders a series of training modules for interpreters on interpreting for dementia.
- 2) Assess the effectiveness of the training modules through a randomized control trial.
- 3) Monitor and evaluate the implementation of the training modules across the Victorian interpreting sector.

Once this project is complete, the training modules will be made available to every accredited interpreter in Australia. The training modules will be maintained on our industry partner, the NAATI website and will be integrated in the mandatory Continuing Professional Development (CPD) for interpreters. Interpreters will be able to access and complete the training at any time.

## 1.3 *Background information*

Australia has an ageing migrant population. With the number of CALD Australians diagnosed with dementia increasing each year, there is growing demand for language interpreters for cognitive assessments and dementia-related health consultations. In order to ensure accuracy and impartiality, NHMRC (National Health and Medical Research Council) Dementia Clinical Guidelines specify that a professional interpreter should be used during cognitive assessments with an older person whose first language is not English [1]. Use of professional interpreters rather than informal interpreters is known to facilitate greater

accuracy, better communication, higher satisfaction from clients and clinicians, and can mitigate concerns that interpretation by non-professionals may involve conflicts of interest [2, 3].

However, even professional interpreters can influence assessments, although the reasons are poorly understood [4-6]. Interpreting for cognitive assessments requires a high degree of accuracy in communicating specific questions, instructions, and/or medical terminology to clients. Communication with cognitively impaired clients can also pose specific challenges, as participants often rely on extra-verbal bodily gestures, facial expressions, and timing to maintain a focused interaction [7-9]. Furthermore, some CALD patients have low health literacy and require reassurance and support in understanding the purpose and process of undertaking a cognitive assessment [5, 6]. Professional interpreters face uncertainties in how to negotiate these demands [8], potentially leading to communication that compromises assessment accuracy and/or creates misunderstanding between patients and clinicians [3, 9]. A lack of specific training in dementia means interpreters may not have the skills for communicating with cognitively impaired patients, knowledge of cognitive assessments, and an understanding of their role in assessments [4, 6, 8, 9].

Prior work by members of this project's research team has identified a demand for specialized training in dementia for interpreters. We have found that difficulties in translation and interpretation contribute to delayed diagnoses of dementia and delayed uptake of health and care services [10]. Cognitive Dementia and Memory Services (CDAMS) and Aged Care Assessment Services (ACAS) rely on hospital- and community-based interpreters when assessing non-English proficient clients [11]. However, interpreting services in Australia are subject to supply and demand imbalances, inconsistent quality of services, and lack of availability in regional areas [12, 13]. This means that while some CDAMS and ACAS can access hospital interpreters in some languages, many assessment services (especially in regional and rural areas) must rely on community interpreters to interpret cognitive assessments for dementia.

In Australia, there currently exists no specialized training for community interpreters working with clients living with dementia or undergoing cognitive assessment. A community-based interpreter workforce familiar with dementia and dementia assessments will be required to meet the growing demand for assessments owing to ageing migrant population. For many community interpreters, dementia-related medical appointments and aged care assessments are a regular source of work. Specialized interpreter training in dementia and cognitive assessments will, we argue, ensure these interpreters are confident and prepared when servicing this clientele. The training will also support the overall accuracy and validity of cognitive testing for older people from CALD backgrounds.

## 2 Study objectives

### 2.1 *Project aims*

The MINDSET project's aims are:

1. To improve the quality of interpreter communication in cognitive assessment for dementia.
2. To implement the training in Victoria, assessing for scalability and services' satisfaction.

We will achieve our project aims by conducting three studies (Fig.1):

#### *Study 1*

Co-design the online training modules with interpreters, clinicians, and carers of CALD people with dementia via co-design workshops (Aim 1).

#### *Study 2*

Undertake a national randomised control trial (RCT) with 150 interpreters to assess in the impact of online training on the quality of interpreter communication in comparison to wait-list control (Aim 1).

#### *Study 3*

Implement the training in Victoria focusing on scalability and assess services' satisfaction with the training via qualitative interviews with interpreters, managers, and clinicians to (Aim 2).

Fig.1: MINDSET project

[figure not shown]

## 2.2 *Hypotheses*

Our hypotheses are that:

### *Study 1*

- 1) Interpreters, clinicians, and carers of CALD people with dementia will, together with the research team and industry partners, successfully co-design training modules that improve the quality of interpreted dementia assessments.

### *Study 2*

- 2) Interpreters trained in the MINDSET program will show an improvement in the quality of interpreted communication for dementia assessments at 3 months and 6 months following the intervention, when compared to their baseline scores.
- 3) Interpreters trained in the MINDSET program will show a greater improvement in the quality of interpreted communication for dementia assessments at 3 months and 6 months following the intervention, when compared to the control group's scores.

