## 5 Study 2 – Randomized control trial of training

Study 2 will be a randomized control trial (RCT), conducted to evaluate whether the training package developed during Study 1 fulfils our primary project aim of improving the quality of interpreter communication in a cognitive assessment for dementia. The trial will be a 6-month wait-list RCT with a parallel design, conducted with a target of 150 interpreters in equal allocation (75 in the intervention group and 75 in the control group).

Outcomes will be assessed at baseline ( $t_0$ ), post-intervention (3m after baseline;  $t_1$ ) and follow-up (6m after baseline;  $t_2$ ). The baseline covariates will include characteristics of interpreters (age; sex; ethnicity; location; educational and economic attainments; and NAATI credential status).

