### 5.2 *Randomisation*

Interpreters will be randomised into:

- a) an intervention group ( $n=75$ ) who will use the training package for 6m immediately following the randomisation, or
- b) a wait list control group ( $n=75$ ) who will receive access to the training package six months after randomisation.

This approach was chosen because it involves no deception of participating interpreters, and because both groups of interpreters will eventually have access to the training.

After enrolment in the trial, and before randomisation, participants will complete the simulated battery to measure the primary outcome of quality of interpreted communication. The test outcome will not be provided to the person until an external statistician has done the randomisation procedure (randomisation by minimisation). A researcher at National Ageing Research Institute will provide the test outcome and randomisation outcome (test/control) to the person approximately one week after doing the simulated tests. This ensures that randomisation outcome is independent of baseline scores. In this pragmatic trial, it is not possible to blind participants to group allocation when collecting the post-intervention scores. Hence, this trial is a single-blinded study where outcome assessors will be blinded to allocation.

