In our study, the simulation of ~40 minutes will mimic a typical cognitive assessment of a CALD patient at CDAMS/ACAS (Box 1). The patient and clinician's dialogue will be uniform, pre-scripted, and filmed in the top six languages spoken by older CALD Australians: Greek, Italian, Mandarin, Cantonese, Vietnamese, and Arabic. The interpreter's dialogue is not scripted, and they will be required to interpret and facilitate the assessment as they would in a standard consultation. Interpreters will be asked to click a video record button to record their online simulated consultation (similar to how Zoom meetings are recorded). These simulations will be automatically saved and uploaded, ready for assessment. After completing the simulation, interpreters will complete the questionnaires. Video footage and the questionnaires will be assessed by blinded assessors who are NAATI examiners, seasoned in applying this assessment model regularly. To ensure rigour, CI [name] will train the assessors about the assessment items and each assessor will have their first four assessments double assessed to check for inter-rater reliability. In scenarios where components of the simulation are missing or incomplete, assessors will only award marks to the overall score for sections of the cognitive assessment that were interpreted. Failure to interpret the introductory or concluding component of the assessment will not affect the score.

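### Hypothesis 2 compares trained interpreters only with their own baseline, so task familiarity, feedback or time could meet it with no training effect

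*Protocol*

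**What the plan says.** Section 2.2 of the protocol lists two hypotheses for Study 2 and does not rank them.

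- Hypothesis 2 expects better interpreting quality among those trained, "at 3 months and 6 months following the intervention, when compared to their baseline scores". The control arm plays no part in this contrast.
- Hypothesis 3 says that trained interpreters "will show a greater improvement in the quality of interpreted communication for dementia assessments at 3 months and 6 months following the intervention", this time relative to the control group.

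The lay summary (Section 1.1) repeats the first contrast as a planned analysis: "We will then statistically analyse whether there is an improvement in performance after doing the training". The same sentence goes on to name differences between the groups as well.

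Three further features bear on Hypothesis 2.

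- Sections 1.1 and 5 have both arms assessed at baseline (t0), 3 months (t1) and 6 months (t2).
- Section 5.4 describes a simulation of about 40 minutes in which the patient's and clinician's "dialogue will be uniform, pre-scripted, and filmed in the top six languages". No alternate form or practice run is described.
- Under Section 5.2 a researcher "will provide the test outcome and randomisation outcome (test/control) to the person approximately one week after doing the simulated tests". That is before both repeat assessments, and it applies to both arms.

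**The concern.** A before-and-after contrast in one arm estimates the training effect plus everything else that changes between the two measurements. Here that includes having done the task before, having been told the earlier result, and three or six months of further professional work. The wait-list arm meets the same conditions and is there to remove them, but Hypothesis 2 does not use it.

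At stake is what the trial may claim. If the training has no effect, the report could still state that one of the two Study 2 hypotheses was met, ahead of the Victorian rollout in Study 3. This is not a detail that an analysis plan would settle, because a plan that faithfully tests Hypothesis 2 as worded carries the problem with it.

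**Working it through.** **1. The plan's own figure.** Section 5.5 gives a difference of 1.3, SD 2.5, alpha 0.05, power 80% and 60 per arm. The normal formula, two-sided, is n = 2 × [(1.960 + 0.842) × 2.5 / 1.3]² = 58.1, so 59 per arm. The t-test version gives 59.03, so 60 per arm. The stated 120 is reproduced; power is 81% at 60 per arm and 89% at 75. This calculation supports the between-arm comparison only and says nothing about Hypothesis 2.

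**2. What each contrast estimates.** Let τ be the training effect and g the gain that both arms share from familiarity, feedback and time.

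- Expected change in the trained arm (Hypothesis 2): τ + g.
- Expected change in the control arm: g.
- Difference in change (Hypothesis 3): (τ + g) − g = τ.

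With τ = 0, Hypothesis 2 tests g.

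**3. How often Hypothesis 2 would then succeed.** Assumptions, none of them from the protocol: τ = 0; g of 0.2 or 0.3 SD (0.5 or 0.75 points on the SD 2.5 scale); correlation ρ between visits of 0.5 or 0.7; scores on a baseline or fixed reference. The number of trained interpreters is 60, taken from Section 5.5.

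The SD of change, in units of the score SD, is √[2(1 − ρ)]: 1.000 at ρ = 0.5 and 0.775 at ρ = 0.7. The noncentrality of the paired t-test is g√60 / √[2(1 − ρ)]. Success is the upper tail of a two-sided 0.05 test.

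| Gain g | ρ | Noncentrality | Success at one visit | Success at both visits |
|---|---|---|---|---|
| 0.2 SD | 0.5 | 0.2 × 7.746 / 1.000 = 1.55 | 33% | about 18% |
| 0.2 SD | 0.7 | 0.2 × 7.746 / 0.775 = 2.00 | 50% | about 33–34% |
| 0.3 SD | 0.5 | 0.3 × 7.746 / 1.000 = 2.32 | 63% | about 47% |
| 0.3 SD | 0.7 | 0.3 × 7.746 / 0.775 = 3.00 | 84% | about 74% |

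With no gain, the one-visit rate is 2.5%. The both-visits column is simulated, with equal gain at 3 and 6 months and equal correlation among the three visits. It matters because Hypothesis 2 names both time points.

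Sensitivity at one visit: at ρ = 0.3 the figures fall to 25% (0.2 SD) and 49% (0.3 SD). With 75 trained interpreters and ρ of 0.5 to 0.7 they rise to 40–60% and 73–91%.

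**4. The randomised contrast under the same conditions.** With an equal gain in both arms and 60 per arm, the between-arm test of change rejected in 4.5–5.3% of simulated trials (4,000 per setting), as it should at alpha 0.05.

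**5. Dependence on the z score.** Section 5.4 does not state the reference for the composite z score. If scores were re-standardised across both arms at each visit, a shared gain would cancel, and simulated success of Hypothesis 2 falls below 0.5%. With a baseline or fixed reference, which a change-from-baseline hypothesis needs to be meaningful, step 3 applies.

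**The case against.** The strongest reply is that the design already deals with this. Study 2 is described throughout as a comparison with wait-list control, the sample size rests on the control–test difference, the model in Section 5.6 includes arm, and Hypothesis 3 is the randomised contrast. Nowhere does the protocol say that Hypothesis 2 alone would establish effectiveness. All of this stands, and it confines the point to Hypothesis 2. It does not remove it, because Hypothesis 2 is still listed, unranked, as something the trial sets out to show.

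A reader might infer that the identical script is used at all three visits. Section 5.4 does not say so. Uniform may mean the same across interpreters and languages, and the measures are to be finalised after Study 1, so alternate forms are undecided rather than excluded. The point does not need reuse: familiarity with the task, the returned result and elapsed time would act with a new script too.

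A reader might also infer that giving controls their result shrinks the randomised difference and costs power. The protocol does not support that. Both arms get the same feedback, and an equal gain cancels. Power would fall only if feedback helped controls more than trained interpreters. Nothing in the document suggests this, and the reverse is as plausible if feedback steers trainees to their weak areas. How detailed the returned result is, and hence how large any feedback effect might be, is also unknown.

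**Conclusion.** The point holds for Hypothesis 2 and goes no further. As worded, it can be met without any training effect. Under the stated assumptions the chance is several to many times the nominal rate at a single visit, and it remains material when success is required at both visits. The exact percentages are illustrative: the gain and the correlation are assumed, and the reference for the z score is not stated. The logical defect does not depend on their values. Hypothesis 3 is not biased by a shared gain, and the trial's randomised conclusion is intact. This should be corrected, but it is a matter of which contrast carries the claim, not a fault in the trial's design.

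**What to change.** In Section 2.2, and correspondingly in the lay summary, remove Hypothesis 2 as a test of effectiveness. Report change from baseline descriptively in both arms, and rest the effectiveness conclusion on the between-arm difference in change at 3 and 6 months (Hypothesis 3). The cost is wording only.

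As an optional safeguard, Section 5.2 could send only the allocation at one week and release baseline results to both arms after t2. The reason given there for the timing, that allocation be independent of baseline scores, requires withholding the result only until randomisation and does not require releasing it during follow-up. The cost is a later mailing and a longer wait for feedback. This step would not remove familiarity or time effects from Hypothesis 2, so it does not replace the change of wording.
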